## Methodology

### Aims

This trial investigates whether non-verbal or minimally verbal students with intellectual disabilities, who require AAC, can acquire foundational reading skills through instructions in phonological awareness (sound blending and phoneme segmentation), letter-sound correspondence, shared reading, sight words, and decoding by working systematically and explicitly with the reading program “Lesing for alle” (“Reading for All”). The adapted reading material has been prepared and designed in line on the basis of the research of the evidence-based reading program Accessible Literacy Learning (ALL) [3].

The research questions are as follow:Is there a functional relationship between the use of “Lesing for alle” and increased accuracy of sound blending by students age 6–14 with intellectual disabilities who require AAC?Is there a functional relationship between the use of “Lesing for alle” and improved acquisition of letter-sound correspondence by students age 6–14 with intellectual disabilities who require AAC?Is there a functional relationship between the use of “Lesing for alle” and improved acquisition of phoneme segmentation by students age 6–14 with intellectual disabilities who require AAC?Is there a functional relationship between the use of “Lesing for alle” and improved acquisition of recognition of sight words by students age 6–14 with intellectual disabilities who require AAC?Is there a functional relationship between the use of “Lesing for alle” and improved acquisition of decoding by students age 6–14 with intellectual disabilities who require AAC?Is there a positive and strong correlation between increasing skills from 1–3 to 4–5? Meaning, is there a transfer from lower-level skills (phonological skills) to decoding skills?

As this trial is a multiple single-case design, there were no comparator interventions chosen.

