### Design

This study will be conducted with multiple single-case design with four multiple randomized baselines, where the shortest baseline has two assessments and the largest has five, and the intervention phase has 18 assessments across time. We have recruited 40 students with intellectual disabilities who require AAC.

To evaluate the effectiveness of the intervention effects in this study, the What Works Clearinghouse (WWC) single-case design technical documentation provides appropriate study analysis techniques [20]. Andzik and Chung [8] recommend that researchers follow these quality guidelines for single-case experimental studies to ensure internal validity of the study with reliable measures (Fig. 1).

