#### What data will be generated

There will be data that will say something about the student’s age, gender, diagnosis, IQ, AAC aid, vocabulary and communicative competence (through results from CDI, McArthur-Bates Communicative Development Inventories), results from the assessments, and time used during the intervention. The data will also provide information about the teacher’s and student’s experiences of being part of the project (social validity).

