#### Statistical analysis plans

Generalized estimating equation (GEE) with work matrix of first-order autoregressive factor will be used to the effects of the implementation of the intervention after the baseline assessment. Missing data will be treated as missing at a random mechanism via restricted maximum likelihood. The adopted significance level is 0.0125 (due to the four correlated outcomes, reducing the false discovery rates). For interobserver quality check, we will calculate the interobserver agreement using intraclass correlation (ICC) [55]. There are no plans to conduct additional analyses (e.g., subgroups or adjusted analyses).

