Another issue that has been discussed extensively is the presentation and information of and about the students. Prominent research in the field points out weaknesses in many studies as they lack characteristics of students who participate in such studies. This contributes to the fact that it can be challenging to conclude for whom the interventions work. Thus, we will extract and analyze information about factors such as age, gender, diagnosis, IQ/mental age, and communicative skills. Stigmatization, especially disseminating research results, has also been discussed. How students with intellectual disabilities are portrayed in research data is extremely important, so the data and interpretations of data do not intend to stigmatize this group of students.

Qualitative data from the questionnaire to the teachers will help identify barriers to the successful delivery of the intervention. Feedback about how the reading material fits into the school and teaching will be used to enhance the social validity of the intervention.

For students who do not have verbal speech and require AAC, it is necessary to modify and adapt the assessments. In this study, the modifications include having the students point to symbols, letters, and printed words. Modifications like this can fundamentally change the nature of the task [11]. Therefore, all the modifications that will be executed will be done as carefully as possible to support reader’s interpretation of results and not divert away from the initial purpose of the study design and intervention. There is a need for standardized assessments of both phonological awareness and reading that do not acquire speech responses [11].

There is a need for a standard within reading instructions for students with intellectual disabilities who require AAC. Existing research describes a lack of competence, a lack of expectations, and a lack of evidence-based reading programs, which could be adapted for those who require AAC. Adapting instructions, to meet the needs of students who require AAC, are important as it contributes to overall effectiveness of intervention and results in positive literacy gains [16]. The ability to have verbal speech should not factor as the rationale and the foundational for reading interventions [61].

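### Research question 6 reads a correlation of gains as transfer while no adjusted analyses are planned; differences in general ability could produce such a correlation without any transfer

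*Protocol article*

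**What the plan says.** All references are to the protocol article.

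- **Aims, question 6:** "Is there a positive and strong correlation between increasing skills from 1–3 to 4–5" The next sentence gives the interpretation: "Meaning, is there a transfer from lower-level skills (phonological skills) to decoding skills" Skills 1–3 are sound blending, letter-sound correspondence and phoneme segmentation. Skills 4–5 are sight words and decoding.
- **Aims, comparator:** "As this trial is a multiple single-case design, there were no comparator interventions chosen". All students receive the programme.
- **Statistical analysis plans:** a GEE is named for the intervention effect and an ICC for rater agreement. No method is named for question 6. The section ends: "There are no plans to conduct additional analyses (e.g., subgroups or adjusted analyses".
- **What data will be generated:** the recorded items include "age, gender, diagnosis, IQ, AAC aid, vocabulary and communicative competence", and also time used during the intervention.
- **Discussion:** "we will extract and analyze information about factors such as age, gender, diagnosis, IQ/mental age, and communicative skills". The context is for whom the intervention works.
- **Design:** "We have recruited 40 students with intellectual disabilities who require AAC".

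**The concern.** Questions 1–5 compare each student with their own baseline, and the start of teaching is randomised. Question 6 has neither protection. On the between-student reading it asks whether students who gain more on the phonological tests also gain more on sight words and decoding. Randomising baseline length does not randomise how much a student gains in phonological skill.

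The sample spans ages 6 to 14, and the inclusion criteria set no bounds on the severity of intellectual disability. If abler students, or those with larger vocabularies, learn more of everything taught, the two gains will correlate even when neither skill feeds the other. Because the article equates the correlation with transfer, a positive answer could be reported as a finding about how reading is acquired when it shows only that some students learn faster.

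**Working it through.** The article gives no figure for question 6, so there is none to reproduce. The check asks how large a correlation ability alone could produce.

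**Inputs.** n = 40 (Design). Significance level 0.0125 (Statistical analysis plans), with 0.05 shown as the conventional level; both are taken as two-sided because the article does not say. Assumed, because the article is silent: the share R² of each gain's variance explained by general ability, varied from 0.05 to 0.5; a cut-off of r ≥ 0.5 for a strong correlation; and a reliability of 0.8 for a measured ability covariate.

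**Model with no transfer.** With ability g and independent errors e1 and e2:

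- gain1 = √R² · g + √(1 − R²) · e1
- gain2 = √R² · g + √(1 − R²) · e2

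The true correlation of the gains is then √R² × √R² = R², although neither skill affects the other.

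**Critical value.** r = t / √(df + t²) with df = 40 − 2 = 38. At 0.05, t = 2.024 and r = 0.312. At 0.0125, t = 2.62 and r = 0.391.

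**Unadjusted correlation, simulated trials of 40 students:**

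| R² assumed | Significant at 0.05 | Significant at 0.0125 | Observed r ≥ 0.5 |
|---|---|---|---|
| 0.05 | 6% | 2% | under 1% |
| 0.10 | 9% | 3% | under 1% |
| 0.15 | 15% | 6% | 1% |
| 0.2 | 24% | 10% | 2% |
| 0.3 | 48% | 27% | 7% |
| 0.4 | 74% | 54% | 23% |
| 0.5 | 92% | 81% | 51% |

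**After adjustment for one ability measure of reliability ρ.** The true partial correlation is R²(1 − ρ) / (1 − R²ρ).

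- With ρ = 1 it is 0, and the rate at 0.05 returns to 5%.
- With ρ = 0.8 and R² = 0.4 it is 0.4 × 0.2 / (1 − 0.32) = 0.08 / 0.68 = 0.12, against 0.40 unadjusted.
- With ρ = 0.8 the rates at 0.05 are about 6%, 8%, 11% and 18% for R² = 0.2, 0.3, 0.4 and 0.5.

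Adjustment therefore removes most of the spurious correlation, but not all of it when ability is measured with error.

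**The case against.** **The exclusion may not reach question 6.** A reader might infer that the analysis section fixes the question 6 correlation as unadjusted. The article does not say so. Question 6 is a listed research question, so its analysis is arguably not additional, and the sentence can be read as ruling out extra versions of the GEE. This stands in part: the method for question 6 is unstated, and that silence alone is no fault in a condensed article. But the exclusion is worded without limit, and it sits badly with the Discussion's promise to analyse the same student factors. That promise does not adjust question 6 either.

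**The estimand is not fixed.** The correlation could be meant within students over time, where stable ability confounds much less. This is possible. The between-student reading is more likely because sight words and decoding are tested at only a few time points, whereas skills 1–3 are tested monthly.

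**The size is assumed.** A reader might infer that the correlation will be spurious. Nothing in the article supports a value of R². The gains come from short four-choice tests, several with 10 items, and error in gain scores would lower it. At R² of 0.05 to 0.10 the excess over the nominal 5% is small. Question 6 also asks for a strong correlation, not merely a significant one, and r ≥ 0.5 is uncommon until R² reaches about 0.4. This objection stands and limits the claim to what ability can do.

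**The covariates may not all be baseline values.** Recruitment places the communicative inventory before baseline. No timing is given for IQ, so it cannot be assumed to have been measured before teaching starts.

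**Adjustment does not prove transfer.** This is true, which is why the wording of question 6 needs to change as well as the analysis.

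**Conclusion.** The concern holds in limited form. As written, question 6 gives a causal reading to what is probably a between-student, observational correlation. The only statement on adjustment excludes it, and the Discussion points the other way.

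The consequence ranges from negligible (6% significant at 0.05 if ability explains 5% of gain variance) to severe (92% if it explains half). It rests on an assumed R², equal influence of ability on both gains, all 40 students analysed and the between-student reading. On the stricter criterion of r ≥ 0.5, itself an assumed cut-off, the range over R² = 0.2 to 0.5 is 2% to 51%. The article does not show where in these ranges the trial lies.

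The weight is minor to moderate: question 6 is affected, and the primary effect analyses are not.

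**What to change.** 1. In Statistical analysis plans, exempt question 6 from the exclusion and reconcile that sentence with the Discussion's statement that student factors will be analysed.
2. State whether question 6 is meant between or within students. If between, pre-specify a partial correlation, or a regression of the sight-word and decoding gain on the phonological gain. Adjust for a short list: IQ or mental age (if measured before the intervention), inventory vocabulary, age, and either randomised baseline group or recorded teaching time. Report the unadjusted value beside it.
3. In Aims, reword question 6 so that either result is called an association, not evidence of transfer.

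**Cost.** A few sentences and no new tests, since these items are already among the data to be recorded; the date of the IQ assessment needs confirming. Three student covariates plus teaching time use 4 degrees of freedom (38 − 4 = 34 remain). With baseline group instead, its three indicators bring this to 6 (38 − 6 = 32 remain). Dropout would reduce these further. The adjusted correlation can be expected to be smaller than the unadjusted one if ability drives both gains.

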#### Video coding

As mentioned earlier, within each phase, 20% of the recorded films will be randomly selected and evaluated by two external raters at item-level across the five primary outcomes. Agreement between the two raters and the teachers will be checked, and in case of agreements below 80%, all the films will be checked. The research assistant will be blinded to when the intervention will start for each student. We have operationalized all aspects of the testing, drew up observation criteria, and made a check list that will be followed when observing the videos. The teachers will record answers during the testing, and the researcher and the researcher assistant score the films blinded for each other on the basis of the checklist in order to calculate the interobserver agreement.

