#### Assessment of the outcomes

A registration form has been developed to use during the assessment and data collection of outcomes. The form is designed so the teacher can click whether the student answers options 1, 2, 3, or 4. It is the student’s teacher who will carry out all the tests. The teacher must register correct or incorrect responses during the assessment. Only the teacher and the student will be present during the testing, and all test situations will be filmed. Each student will receive an individual follow-up plan that will describe in detail when tests will be carried out and when the intervention will start. Within each phase, 20% of the recorded films will be randomly selected and evaluated by two external raters at item-level across the five primary outcomes. Agreement between the two raters and the teachers will be checked, and in case of agreements below 80%, all the films will be checked.

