#### Blinding

This is an open-label trial because it is impossible to mask the students when the intervention starts (baseline). Moreover, given that the first author of this manuscript is the research leader of the project, she will coordinate the field work and will act as one of the assessors based on her training on the assessment of the outcomes and intervention and thus will not be able to remain blinded from the study subjects. Since all the 18 assessments across time will be filmed after the agreement and reliability were checked by two assessors, the teachers will not be blinded on which phase of the intervention the students are assigned. However, the two assessors will code the outcomes independently to establish interobserver agreement on the coded observations.

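### The film check on unblinded teacher scoring names two incompatible pairs of raters, one including the unblinded project lead, and its 80% agreement rule need not detect intervention-phase over-scoring of up to about 20% of items

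*Protocol article*

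**What the plan says.** All places are in the protocol article.

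- **Who scores.** *Assessment of the outcomes*: "It is the student’s teacher who will carry out all the tests". The teacher also records each response as correct or incorrect, with only teacher and student present. *Setting of the study* has the same teachers deliver the programme. *Blinding*: "the teachers will not be blinded on which phase of the intervention the students are assigned".
- **Who checks, first statement.** *Assessment of the outcomes*, repeated at the start of *Video coding*: a random 20% of films within each phase is "evaluated by two external raters at item-level".
- **Who checks, second statement.** The end of *Video coding*: "the researcher and the researcher assistant score the films blinded for each other". *Blinding* says of the project lead that "she will coordinate the field work and will act as one of the assessors" and that she cannot remain blinded.
- **Masking of the raters.** *Video coding* states that the research assistant is blinded to when each student's intervention starts. No such statement is made for the other rater. The two raters score blinded to each other, using a checklist.
- **Action rule.** "in case of agreements below 80%, all the films will be checked". No comparison of disagreements by direction or between phases is described. *Statistical analysis plans* adds an intraclass correlation as the interobserver quality check.

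**The concern.** The treatment effect is a contrast between baseline and intervention scores within students, and the person recording those scores knows the phase and is teaching the programme. Teacher error that is the same in both phases largely cancels out of that contrast. Error that favours the student only once the programme has begun does not cancel, and it looks exactly like a treatment effect. The film re-scoring is what could reveal it.

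Two features weaken that check. First, the article gives two different answers to who the raters are. Under one of them, a rater is the person who leads the project, co-developed the tests, enrols the students, collects the memory cards and receives the teachers' monthly summaries. She is neither external nor blinded, and she could share the teachers' expectation. Second, the only rule that leads to action counts disagreements without regard to sign. Ten disagreements scattered in both directions and ten that all credit the student in the intervention phase count the same.

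**Working it through.** **1. The rater statements side by side.**

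| Section | Film raters | Masked to phase? |
|---|---|---|
| *Assessment of the outcomes*; start of *Video coding* | two external raters | not stated |
| End of *Video coding* | the researcher and the research assistant | assistant: blinded to intervention start; researcher: not stated |
| *Blinding* | project lead is one of the assessors | lead: no |

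The first row cannot hold together with the other two. Reading the researcher in *Video coding* as the project lead is an inference, but *Blinding* supports it directly.

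**2. Largest one-directional shift that still meets the rule.** The 80% is a rule, so there is no stated figure to reproduce. Shift = (1 − 0.80) × number of items. Test lengths are from *Primary outcomes*.

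- Sound blending and phoneme segmentation: 0.20 × 10 = 2 points
- Letter-sound correspondence: 0.20 × 25 = 5 points

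**3. That shift as an effect size.** d = shift / SD. The article gives no SD, so a range is assumed for a 10-item score. The last column is the agreement left by a bias worth exactly d = 0.5, which is 1 − (0.5 × SD)/10. The planning effect of d = 0.5 is from *Sample size calculation and power*.

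| Assumed SD (points) | d for 2 points | Agreement when bias is d = 0.5 |
|---|---|---|
| 1.5 | 2/1.5 = 1.33 | 92.5% |
| 2 | 2/2 = 1.00 | 90% |
| 3 | 2/3 = 0.67 | 85% |
| 4 | 2/4 = 0.50 | 80% |

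Throughout this range, a bias as large as the planning effect leaves agreement at or above the threshold.

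**4. Number of films.** *Design* gives 2 to 5 baseline assessments and 18 in the intervention phase. *Primary outcomes* can be read as 18 in total.

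- 18 in total: 40 × 18 = 720 films, and 20% is 144.
- 18 in the intervention phase, baseline averaging 3.5 (lengths 2, 3, 4, 5 in equal groups): 40 × 18 = 720 and 40 × 3.5 = 140. The 20% samples are 144 and 28, together 172.

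**5. How often the rule fires.** Take one 10-item test on 144 intervention films, so N = 1,440 items. Assume independent items and a true share q of items that disagree. The rule fires when more than 0.20 × N = 288 items disagree, and the probability is binomial.

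| q, all in one direction | P(rule fires) |
|---|---|
| 10% | about 0 |
| 15% | about 0 |
| 18% | 0.02 |
| 20% | 0.48 |
| 22% | 0.97 |
| 25% | about 1 |

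The rule therefore works as a cut at about 20% of items. If agreement were instead pooled over both phases with no baseline disagreement, intervention-phase disagreement would need to reach 0.20 × 172/144 = 23.9% before it fired.

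**6. Why the order of the films matters.** *Recruitment* has baseline starting in the same week for all students. With baselines of two to five assessments taken in sequence, assessments 1 and 2 are baseline for everyone and assessment 6 onward is intervention for everyone. Only assessments 3 to 5 differ by group. A rater who does not know a student's start date but can see a film's month would still know the phase for most films.

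**The case against.** The strongest reply is that scoring leaves little room for leniency. Each item is a choice among four options with a predetermined target, the form records which option was chosen, a checklist with observation criteria exists, and every test is filmed. One rater is blinded to intervention start and the two score independently, so a lead who shared the teachers' bias would tend to disagree with the assistant. Sampling within each phase means agreement could be examined by phase. All of this stands. It makes large bias less likely and means that the film check is not the only safeguard. It does not settle who the raters are, it leaves one of them unmasked on the second reading, and the article states no comparison by phase or direction.

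Four stronger claims are tempting, and the document does not support them.

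- A reader might infer that the 80% rule cannot detect scoring that favours the intervention. It can: at 22% one-directional disagreement it fires with probability 0.97 under the assumptions above.
- A reader might infer that high chance agreement late in the trial disables the rule. That treats the scorers as independent, but they score the same pointing response. Where 90% of items are truly correct, over-scoring can add at most one point in ten.
- A reader might see percent agreement and the intraclass correlation as contradictory. One triggers full checking and the other is a quality summary, so they can coexist.
- A reader might conclude that neither rater is masked. The assistant is stated to be.

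It is also fair to say that the 2-point figure is a worst case: every permitted disagreement in one direction, confined to one phase.

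**Conclusion.** The point holds in two parts. The contradiction over the raters is plain in the text and needs only the inference that the researcher who scores films is the project lead named as an assessor. The weakness of the action rule is one of size: it need not detect intervention-phase over-scoring of up to about 20% of items, which is 2 points in 10 or 5 in 25. For a 10-item test that is d of 0.5 to 1.33 if the SD is 4 to 1.5 points, so it equals or exceeds the planning effect of 0.5 across that range. The effect-size range rests on the assumed SDs, and the firing probabilities rest on independent items and 144 intervention films.

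Nothing here shows that teachers will over-score, and the trial is not invalidated. As written, though, a positive result would be open to a scoring-bias explanation that the stated check could miss. It should be put right.

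**What to change.** 1. Reconcile *Assessment of the outcomes*, *Blinding* and *Video coding* so that both film raters are the external raters already promised and the project lead does not score films.
2. Give both raters films relabelled with neutral codes and shuffled across months and students, so that neither is told the phase.
3. Keep the 80% rule and, alongside it, report the signed teacher-minus-rater score difference for each test, separately for baseline and intervention. A difference near zero in both phases answers the scoring-bias objection. One that appears only in the intervention phase shows how much of the effect it could explain.

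The cost is small: relabelling and one further tabulation on the sample already planned, about 144 films if there are 18 assessments in total and about 172 if all 18 fall in the intervention phase. No additional films need to be scored. Masking will not be perfect, since a student's progress may hint at the phase, but it removes the direct knowledge that the present wording allows.
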